## Abstract

**Background:**

Systematic reviews have identified a range of brief interventions which increase physical activity in previously sedentary people. There is an absence of evidence about whether follow up beyond three months can maintain long term physical activity. This study assesses whether it is worth providing motivational interviews, three months after giving initial advice, to those who have become more active.

**Methods/Design:**

Study candidates (n = 1500) will initially be given an interactive DVD and receive two telephone follow ups at monthly intervals checking on receipt and use of the DVD. Only those that have increased their physical activity after three months (n = 600) will be randomised into the study. These participants will receive either a "mini booster" (n = 200), "full booster" (n = 200) or no booster (n = 200). The "mini booster" consists of two telephone calls one month apart to discuss physical activity and maintenance strategies. The "full booster" consists of a face-to-face meeting with the facilitator at the same intervals. The purpose of these booster sessions is to help the individual maintain their increase in physical activity. Differences in physical activity, quality of life and costs associated with the booster interventions, will be measured three and nine months from randomisation. The research will be conducted in 20 of the most deprived neighbourhoods in Sheffield, which have large, ethnically diverse populations, high levels of economic deprivation, low levels of physical activity, poorer health and shorter life expectancy. Participants will be recruited through general practices and community groups, as well as by postal invitation, to ensure the participation of minority ethnic groups and those with lower levels of literacy. Sheffield City Council and Primary Care Trust fund a range of facilities and activities to promote physical activity and variations in access to these between neighbourhoods will make it possible to examine whether the effectiveness of the intervention is modified by access to community facilities. A one-year integrated feasibility study will confirm that recruitment targets are achievable based on a 10% sample.

**Discussion:**

The choice of study population, study interventions, brief intervention preceding the study, and outcome measure are discussed.

**Trial Registration:**

Current Controlled Trials: ISRCTN56495859; ClinicalTrials.gov: NCT00836459.

## Background

There are a number of published systematic reviews of evidence for interventions that increase physical activity [1-5]. More recently the evidence base for brief interventions in primary care has been reviewed [6]. This review identified a sufficient evidence base for NICE to recommend the use of brief interventions to promote physical activity but also identified specific evidence gaps that this trial will be able to address, particularly in relation to the value of follow up beyond three months, for the longer term maintenance of physical activity.

Searches of the National Research Register and ClinicalTrials.gov for research in progress confirm that, although there are a number of physical activity intervention trials in progress in specific patient groups and in older age groups or in children, there are few trials including "healthy" middle-aged participants and no other trials specifically examining the value of further intervention after an initially successful "brief intervention".

The Sheffield Physical Activity Booster Trial is a three-arm, parallel group, randomised controlled trial with a feasibility study. It will compare two different intensities of Motivational Interviewing (MI; 'booster') intervention against no further intervention in people who have already increased their physical activity levels following a brief intervention. The "mini booster" of two telephone physical activity consultations and a "full booster" of two face-to-face physical activity consultations will be offered four and five months after the initial brief intervention. The purpose of these booster sessions is to help participants to sustain their physical activity levels and prevent relapse. The brief intervention will involve provision of an interactive DVD based on a MI approach that is directive, client-centred and replicates the style of other successful behaviour change programmes [7,8]. All interventions, including the initial brief intervention, will be delivered by trained facilitators (employed as research assistants and trained by the research team) to ensure consistent delivery.

## Methods/Design

### Participants

We are working with local health services to identify potentially eligible study candidates. NHS Sheffield will send a letter with postage-paid reply card to at least 30,000 people to inviting them to enrol in a programme to help them get more physically active. This programme involves a "brief intervention" (interactive DVD), which is consistent with NHS guidance on physical activity and behaviour change interventions [6,9]. Research assistants will telephone respondents and administer the Scottish Physical Activity Questionnaire (SPAQ)[10]. Those eligible to receive the brief intervention (DVD) will be: (1) residents of the 20 most deprived neighbourhoods in the city of Sheffield; (2) aged 40 to 64 years; and, (3) not achieving the current recommended activity level (30 minutes of moderate activity on at least 5 days) assessed using the SPAQ and wishing to have support to become more active. Those subsequently eligible for participation in the trial will also: (4) have increased their physical activity level by at least 30 minutes of moderate or vigorous activity per week (assessed using the SPAQ) over the three-month brief intervention (DVD) period; and, (5) be capable of giving written informed consent to trial participation. Individuals with chronic conditions who can benefit from physical activity will not be excluded unless their condition significantly impairs their ability to exercise. They will be asked to consult their GP if they have a condition that increases their risk of adverse events during exercise (e.g. chronic cardiovascular or pulmonary disease). Participants may withdraw from active participation in the study on request. If a participant experiences chest pain or severe breathlessness during the 12-minute walk test (see below), then the researcher will advise the GP directly and immediately, and will also advise the participant to make an appointment with their GP at their earliest convenience. Subjects removed from active participation will not be replaced and, with their consent, will be followed up for all outcome information.

### Booster Interventions

Candidates deemed eligible after a telephone assessment will be invited to attend a baseline assessment appointment at a community venue and they will be randomly allocated to one of three groups:

1. a "full booster" group (n = 200) receiving an intervention comprising two face-to-face physical activity consultations, delivered in a motivational interviewing style, at one month and two months from randomisation;

2. a "mini booster" group (n = 200) also receiving an intervention comprising two telephone-based physical activity consultations, delivered in a motivational interviewing style, at one month and two months from randomisation; or,

3. a control group (n = 200) who will be assessed at randomisation, after three months and after nine months and receive no additional intervention between those assessments.

Participant flow through the study from initial contact to final follow-up is illustrated in figure 1.

**Figure 1 F1:**
[figure not shown]
**Participant flow through the study**.

The "full" booster will comprise two 20-30 minute face-to-face physical activity consultations that aim to promote and sustain change in physical activity status. These will take place in community venues. The consultation will be underpinned by the principles of the Trans-Theoretical Model (TTM) of behaviour change and replicate a brief version of motivational interviewing based on a method designed for time limited consultations in medical settings [11,12]. Such an approach has been successfully employed to change health-related behaviours previously [13]. This approach also mirrors that adopted by the health trainer initiative which provides a current model of face-to-face promotion of healthy behaviours. For the "full" booster, a menu of six strategies has been developed to guide the 30-minute consultation. Each strategy is suitable for participants who are in the maintenance stage of motivational readiness for physical activity behaviour change. They are: 1. assessment of motivation and confidence for maintaining physical activity; 2. increasing knowledge of the benefits of physical activity and the risks of a sedentary lifestyle, and increasing awareness of physical activity opportunities and the current recommendations for physical activity; 3. increasing confidence to be physically active - self-efficacy; 4. goal setting and tracking using SMART (specific, measurable, achievable, realistic, time-related) goal principles; 5. strategies for staying motivated; and, 6. relapse-prevention strategies. During the "full" booster consultations, strategies will be worked through at a pace dictated by the participant and the menu used to structure information exchange without being prescriptive.

Although face-to-face interventions have been found to be efficacious in promoting physical activity, many of the barriers associated with this approach, including time and financial costs, highlight the need for pragmatic alternatives that are both relatively cheap to deliver and may make it easier for the participant to access the intervention [13]. The "mini" booster will consist of two 20-30 minute telephone based physical activity consultations. The telephone consultation will follow the same menu of six behaviour change strategies as the "full" booster (outlined above) and aim to promote and sustain change in physical activity status. A number of studies using telephone support for physical activity in older adults have been carried out [3,14]. A telephone-based approach has been effective in increasing physical activity participation at six months compared to no telephone support and has also been shown to increase physical activity participation to a greater extent than standard reading materials in adult populations [14,15]. The telephone consultations will follow a script of known efficacy that has been implemented in previous physical activity promotion studies delivered by members of this research team.

The MI training and interventions will follow a treatment fidelity framework, based on the Behaviour Change Consortium, to ensure reliability and consistency of the approach [16,17]. This framework provides quality assurance parameters based on the intervention design, training, delivery, receipt and enactment. A recent review [16,17] highlighted inconsistent delivery and varying levels of competence among physical activity interventionists reporting to deliver a physical activity counselling components. It suggested that the effectiveness of behaviour change counselling is predicted by the length, the intensity, the content of interventions and the competence of the deliverer [17]. The sessions will therefore be delivered by a team of six research assistants (RAs) trained in MI and behaviour change techniques and assessed to ensure their competency. A framework will be developed for each session to ensure consistency of advice across sessions and between participants. All RAs will be trained (by [name]) using a training package and a detailed manual to ensure standardised delivery of the booster interventions. All booster interventions will be video-recorded. A random selection of 5% of all booster consultations (10 telephone and 10 face-to-face) will be reviewed and assessed by an independent clinical psychologist using a pre-determined check list. The RAs will be provided with individual feedback if required, to ensure intervention fidelity is maintained.

### Objectives

The overall aim is to measure the effectiveness and cost effectiveness of "mini" and "full" booster sessions, as an adjunct to a brief intervention, in sustaining physical activity in middle-aged adults. The primary objective is to determine whether physical activity, measured by accelerometry three months after randomisation (six months after a brief intervention), is significantly increased in participants allocated to two intervention groups ("full" or "mini" booster) compared to participants allocated to a control group (receiving no further contact after the baseline assessment). Secondary objectives are as follows:

1. To determine whether physical activity nine months after randomisation (12 months after the brief intervention) is significantly increased in participants allocated to the two intervention groups compared to participants allocated to the control group.

2. To compare physiological measures of fitness (12 minute walk test) and self-reported physical activity (SPAQ) between allocated groups.

3. To compare health related quality of life, resource use (including health and social care contacts) and economic costs between allocated groups.

4. To investigate whether the impact of the intervention may be modified by gender, ethnicity or the types of physical activity undertaken (including use of community facilities for physical activity).

5. To undertake a process evaluation to identify, using both quantitative and qualitative methods, psychosocial and environmental factors that may mediate or modify the effectiveness of the intervention (this aspect of the study is the subject of a separate protocol and is not discussed further here).

### Outcomes

The timing of all outcomes relative to the point of randomisation is shown in Table 1. The primary outcome is seven-day accelerometry, using Actiheart (CamNtech, Cambridge, UK), measured at three months and nine months post-randomisation (see Discussion). Secondary outcomes are:

**Table 1 T1:** Timing of procedures and assessments

	Minus 3 months	Minus 2 months	Minus 1 month	~Minus 1 week	Randomisation	1 month	2 months	3 months	9 months
Brief Intervention Screening Checklist	✔								
SPAQ	✔			✔				✔	✔
DVD (if eligible)	✔								
DVD usage assessment		✔	✔						
Booster Trial Screening Checklist				✔					
Participant Information Sheet				✔	✔				
Participant Consent Form					✔				
BREQ-2					✔			✔	✔
EXERT					✔			✔	✔
Questionnaire 1					✔				
Questionnaire 2					✔			✔	✔
Questionnaire 3 (SF-12v2+4)					✔			✔	✔
Height & weight					✔			✔	✔
Randomisation					✔				
Booster intervention (Rx only)						✔	✔		
12 minute walk test								✔	✔
7 day accelerometery								✔	✔

1. Self-reported moderate or vigorous physical activity using the Scottish Physical Activity Questionnaire (SPAQ) which records type and duration of activities in the previous week;

2. Behavioural Regulation in Exercise Questionnaire (BREQ-2) [18];

3. Exercise Evaluation Randomised Trial (EXERT) questionnaire [19];

4. Health-related quality of life using the Sheffield Version of the 16-item Short Form health survey instrument (SF-12v2 plus 4);

5. Self-reported use of community facilities for physical activity;

6. Self-reported health and social care contacts;

7. Body mass index; and,

8. The 12 minute walk test (physiological measures of fitness) [20].

### Sample size

For the purposes of sample size estimation the primary outcome is an objective measure of physical activity and will be the mean physical activity levels from the 7-day accelerometric assessment (recoded as counts per week) at 3 months post-randomisation (6 months after initial contact). Kirk and colleagues suggest a standard deviation of approximately 1.2 million counts per week from a 7-day accelerometer assessment of 70 patients with type II diabetes [21]. We assume a mean difference of 400,000 counts per week between the intervention and control groups is the smallest difference of clinical and practical importance that is worth detecting. With 450 subjects (300 intervention: 150 control), the trial will have 90% power to detect this mean difference or greater between the "booster" arm and control arm (assuming a standard deviation of 1.2 million counts/week) as statistically significant at the 5% (two-sided) level using a two independent samples t-test.

With 300 subjects in the booster intervention (150 "mini": 150 "full" booster) the trial will have also have approximately 80% power to detect a similar mean difference of 400,000 counts per week between the two booster arms as statistically significant at the 5% (two-sided) level using a two independent samples t-test. Assuming an approximate 25-30% loss to follow-up by six-months, we proposed to recruit and randomise 200 subjects per group (600 in total). We will invite at least 30,000 40-64 year olds from the 20 most deprived neighbourhoods; we expect at least 1500 will receive the brief intervention of which we anticipate at least 40% will increase their physical activity and be eligible for randomisation. N = 600 divided equally between the three trial arms (200 per arm).

### Randomization sequence generation

The allocation schedule is generated prior to the study by the Sheffield Clinical Trials Research Unit. The randomisation sequence is computer-generated.

### Allocation concealment

The allocation schedule will be concealed through the use of a centralised web-based randomisation service.

### Implementation

During the baseline visit, after informed consent has been obtained, the research assistant will telephone the study manager or data manager, who will randomise the participant. The research assistant will inform the participant of the treatment allocation and the study team will inform their general practitioner that they have been recruited to the study.

### Blinding

Data analysts will be blind to treatment allocation, but the study manager, research assistants and participants (who are also outcome assessors) will not be blinded.

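### Research assistants are unblinded and deliver the boosters, and no separate assessor is named, so a participant's own counsellor may run that participant's follow-up walk test and SPAQ

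*Protocol article*

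**What the plan says.** Under Blinding, the protocol article masks only the data analysts and states that "the study manager, research assistants and participants (who are also outcome assessors) will not be blinded".

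Other sections show what the research assistants do:

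- **Boosters.** Under Booster Interventions: "The sessions will therefore be delivered by a team of six research assistants (RAs) trained in MI and behaviour change techniques". The Background likewise says that all interventions, the initial brief intervention included, are "delivered by trained facilitators (employed as research assistants and trained by the research team".
- **Allocation.** At the baseline visit the assistant telephones for the randomisation, and then, under Implementation, "The research assistant will inform the participant of the treatment allocation".
- **SPAQ.** Under Participants, for screening: "Research assistants will telephone respondents and administer the Scottish Physical Activity Questionnaire (SPAQ". Under Outcomes the SPAQ is a self-report "which records type and duration of activities in the previous week".
- **Walk test.** The only mention of staff is under Participants, on symptoms during the test: "then the researcher will advise the GP directly and immediately". The role of this researcher is not specified.

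Table 1 places the walk test at three and nine months only. It places the SPAQ at screening, about one week before randomisation, and at three and nine months. Both belong to secondary objective 2. The primary outcome is seven-day accelerometry.

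**The concern.** The walk test depends on effort and can respond to encouragement from whoever supervises it. The SPAQ is recalled, and when staff administer it the answers can lean towards what the participant thinks the questioner hopes to hear. If that questioner has just given the participant two consultations on staying active, both measures may be pushed up in the booster arms. The push may also differ between the full booster (face to face) and the mini booster (telephone).

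Two features make these outcomes sensitive. The walk test has no baseline value, so a difference at follow-up cannot be adjusted for the participant's own starting point. The SPAQ is the only activity measure in Table 1 taken both before randomisation and at follow-up, so the planned comparison of proportions maintaining or increasing their weekly activity appears to depend on it. A favourable result on either could not be separated from assessor influence.

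Not blinding the assistants is a stated choice, not a detail left to a fuller document. Participants cannot be blinded to a counselling intervention, but who assesses them can be arranged.

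**Working it through.** **1. The passages side by side.** The assistants know allocations (Blinding, Implementation) and are the counsellors (Background, Booster Interventions). No other assessment team is named. The bracket in the Blinding sentence can be read in two ways:

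- If it covers the assistants, unblinded counsellors assess outcomes.
- If it covers participants only, which is the more natural reading, it suits self-reported outcomes but not the walk test, at which a researcher is present. The walk-test assessor is then unnamed, and the only field staff described are unblinded.

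On neither reading does the article keep counselling and assessment of the same participant apart.

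**2. The plan's own figures.** Inputs from Sample size: 300 booster and 150 control analysed, difference 400,000 counts per week, SD 1.2 million, two-sided 5%.

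- SE in SD units = √(1/300 + 1/150) = 0.10.
- Standardised difference = 0.4/1.2 = 0.333, and 0.333/0.10 = 3.33.
- Power = Φ(3.33 − 1.96) = 91.5% (91.4% with the noncentral t), against a stated 90%. This reproduces.
- Recruitment at 25% loss: 450/0.75 = 600, as stated.

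**3. Effect of an assumed bias on a continuous secondary outcome.** With no true effect and a bias of b SD towards the boosters, the two-sided rejection rate is Φ(b/SE − 1.96) + Φ(−b/SE − 1.96).

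| Assumed b (SD) | Boosters v control, 300 v 150, SE 0.10 | Full v mini, 150 v 150, SE √(2/150) = 0.1155 |
|---|---|---|
| 0 | 5.0% | 5.0% |
| 0.05 | 7.9% | 7.2% |
| 0.10 | 17.0% | 13.9% |
| 0.15 | 32.3% | 25.5% |
| 0.20 | 51.6% | 41.0% |

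In the last column b is the difference in bias between the two booster arms. The values of b are assumptions, and the numbers analysed are those planned for three months. The article states no separate loss to nine months.

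**4. Room in the rota.** Six assistants, less the one who ran the baseline visit, less the one or two who gave the boosters, leaves 6 − 1 − 1 = 4 or 6 − 1 − 2 = 3 for a booster participant, if these are different people. For a control it leaves 6 − 1 = 5. Where a bilingual facilitator is needed (Discussion, Choice of study population) there will be fewer.

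**The case against.** A reader might infer that the assistants who give the boosters do run the follow-up assessments. The article does not say so. The SPAQ sentence concerns telephone screening before the DVD, the walk-test sentence says only that a researcher is present, and the bracket may describe participants alone. It may also be said that visit rotas and test scripts belong in the full protocol. This limits the point to what may happen. It does not remove it, because the article itself fixes the assistants as unblinded.

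A reader might also infer that controls have no tie to the assistants, so that the bias can run only one way. That is not supported either. All participants have contact with assistants through screening, the DVD period and the baseline visit. The arms differ by two consultations of 20 to 30 minutes, by telephone only in the mini arm. Bias towards the boosters is the likely direction, not a demonstrated one.

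The percentages would follow for any bias of that size on any outcome with these numbers. They show how sensitive the comparison is and are not evidence that a bias exists. They also do not separate the assessor's share from the participant's. Both objections stand.

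Finally, a rota cannot abolish the problem. Participants know their allocation, so their own recall, wish to please and effort remain whoever assesses them. This too stands.

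**Conclusion.** The point holds as a risk to secondary outcomes. As written, the plan allows an unblinded counsellor to assess that counsellor's own participants on the walk test and on any staff-administered SPAQ, and nothing in the article prevents it. The size of the bias is unknown. On assumed biases of 0.05, 0.10 and 0.20 SD, and the planned 300 v 150, the false positive rate for boosters against control would be about 8%, 17% and 52% instead of 5%.

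It would be wrong to conclude that the primary result is compromised. Accelerometry is recorded by a device and does not rest on an assessor's rating, the analysts are blinded, and the sample size is unaffected. This is a cheap improvement that should be made, not a flaw that invalidates the design.

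**What to change.** Amend the Blinding section to say who conducts the three- and nine-month assessments, on these lines:

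- Where feasible within the existing six, follow-up walk tests and any staff-administered SPAQ are done by an assistant who had no part in that participant's baseline and randomisation visit or boosters, and who is not shown the allocation. Excluding only the booster counsellor is not enough, because the baseline assistant also learns the allocation.
- The walk test follows a standard script in all arms.
- Participants are asked not to mention booster contacts, and any unmasking is recorded.
- The SPAQ is reported as unblinded self-report.

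The cost is one paragraph of text and a tighter rota, with no added staff. Masking will be imperfect. The change reduces the assessor's share of the bias but not the share that comes from participants knowing their own allocation, so the false positive rate returns to 5% only if no bias of the second kind exists.
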